## Abstract

**Background:**

The Taste And Smell To Enhance nutrition (TASTE) trial investigated the effects of smell and taste of milk with tube feeding compared to routine care on the growth of preterm infants. There was no difference between groups in growth (weight, head circumference, length) *z*-scores at discharge from the hospital. Infants in the intervention group had higher head circumference and length *z*-scores at 36 weeks postmenstrual age, both secondary outcomes. The objective of this follow-up study is to assess 2-year neurodevelopmental and growth outcomes after exposure of preterm infants to the smell and taste of milk with tube feeding compared to routine care.

**Discussion:**

For patients and their families, the neurodevelopmental outcomes of preterm infants are of utmost importance. Consequently, they should be investigated following any interventional study performed during the newborn period. Furthermore, improved weight gain and head growth in the hospital are associated with better long-term neurodevelopmental outcomes. Smelling and tasting of milk is an uncomplicated and cost-effective intervention that may improve the growth and neurodevelopmental outcomes of preterm infants. Potential limitations affecting this follow-up study, caused by the COVID-19 pandemic, are anticipated and discussed in this protocol.

**Trial registration:**

Name of the registry: Australian and New Zealand Clinical Trials Registry; Registration number: ACTRN12617000583347; Registration date: 26 April 2017.

## Background

Preterm birth is a strong predictor of poor health outcomes and is associated with long-term neurodevelopmental challenges [1–3]. Clinicians are continuously refining neonatal care to improve long-term outcomes for preterm infants. Optimizing nutrition is a focus as growth failure is a universal problem in this vulnerable population. Improved weight gain and head circumference during the initial hospital admission of preterm infants are associated with improved long-term neurodevelopmental outcomes, as long-term follow-up studies as late as early adulthood have demonstrated [4, 5].

Smell and taste sensations are primarily processed in the olfactory and gustatory cortex and then integrated with higher brain functions [6, 7]. The stimulation of those primary senses activates complex pathways and initiates food anticipation and cephalic phase responses that make up the orchestrated physiological preparation of the body for food intake [8–10]. “Early nutritional learning” describes interactions with food, including smells, tastes, and emotions around feeding that modify appetite and satiety development and the rate of weight gain [10–13]. It occurs during a time of brain development that is marked by rapid neuronal proliferation, myelination, and synaptogenesis and is known to generate the long-term basis for food preferences and eating behavior with effects seen even into adulthood [14–17]. Research into the long-term effects of early nutritional experiences is sparse but investigating the potential impact on cognitive outcomes has been suggested [18].

The Taste And Smell To Enhance nutrition (TASTE) trial evaluated the effects of smell and taste of milk with tube feeding versus routine care in preterm infants on weight at discharge [19]. A total of 396 infants born at less than 29 weeks postmenstrual age and/or with a birth weight of less than 1250 g were randomized to either smell and taste of milk with each tube feeding or routine care. It concluded that preterm infants with the provision of regular smell and taste of milk with a tube did not have higher growth (weight, length, head circumference) *z*-scores at discharge home from the hospital. In prespecified secondary analyses, we found that the intervention group had higher head circumference and length *z*-scores at 36 weeks postmenstrual age.

Smell and taste with tube feeding have no known side effects, require little extra time, and are easy to apply, with minimal costs. Given that late gestation and early infancy is a crucial time for brain development, nutritional learning experiences may be part of the more general neurodevelopmental journey of an infant [20–22].

With the additional observation in mind that infants in the TASTE trial’s intervention group have improved head circumference at 36 weeks postmenstrual age, a neurodevelopmental follow-up study of newborn infants exposed to oropharyngeal colostrum or smell and taste of milk, compared to routine care, is warranted. Moreover, for patients and their families, the neurodevelopmental outcomes of preterm infants are of utmost importance and should be investigated as part of any neonatal interventional study. The current follow-up study aims to assess long-term effects on neurodevelopment at 2 years corrected age (CA) of exposure to smell and taste of milk with tube feeding versus routine care in infants born at less than 29 weeks postmenstrual age and/or with a birth weight of less than 1250 g.

## Methods

### Study design

This is a follow-up study of a clinical, non-blinded, parallel-group randomized superiority trial (TASTE trial, ACTRN 12617000583347) [19]. The TASTE trial recruited participants between May 2017 and February 2020 at two Australian sites: the Mater Mothers’ Hospital in Brisbane, Queensland, and the Royal Women’s Hospital in Melbourne, Victoria. With parental consent, infants born at less than 29 weeks postmenstrual age or with a birth weight of less than 1250 g were randomized to receive the smell and taste of milk with tube feeding (intervention group) versus tube feeding alone (control group) until they were fully suck feeding or until discharged from hospital. A total of 396 infants were randomized: 196 were assigned to the intervention group, and 200 were assigned to the control group. No between-group differences were observed for the primary outcome, weight *z*-score at discharge [19]. However, in prespecified secondary analyses, head circumference and length *z*-scores were significantly higher in the intervention group at 36 weeks postmenstrual age.

Neurodevelopmental and growth outcomes were listed as secondary outcomes in the original TASTE trial protocol [23]. The current protocol for the 2-year follow-up study defines impairment classifications for outcomes and the statistical analysis as well as takes into account the anticipated impact of the COVID-19 pandemic, details not available in the original protocol. This follow-up protocol does not describe the original trial's randomization, intervention, or discontinuation or modification of the allocated intervention; those details can be found in the original TASTE trial protocol [23].

### Study setting

Participants who were enrolled in the TASTE trial as newborn infants and randomized to either smell and taste of milk with tube feeding or routine care had their neurodevelopmental outcome assessed at 2 years CA (defined as 2 years from the date the infant was expected to be 40 weeks gestation). There was no anticipated harm and no compensation for trial participation or provision for post-trial care. Data collection for this follow-up study was impacted by the COVID-19 pandemic, and therefore, the CONSORT and SPIRIT Extension for RCTs Revised in Extenuating Circumstances (CONSERVE 2021) is followed for the current protocol. The follow-up study was performed within the routine neonatal follow-up programs of the Mater Mothers’ Hospital in Brisbane and the Royal Women’s Hospital in Melbourne. Follow-up commenced in August 2019 and concluded in October 2022.

### Eligibility

Surviving infants who participated in the TASTE trial and were eligible for a routine clinical neurodevelopmental assessment qualified for inclusion in this follow-up study. In agreement with the Australian and New Zealand Neonatal Network recommendations, infants born at less than 28 weeks postmenstrual age and/or less than 1000 g birth weight are eligible for routine neurodevelopmental follow-up at 2 years CA [2]. No additional funding was available to ensure neurodevelopmental follow-up for TASTE trial participants who did not meet the Australian and New Zealand Neonatal Network criteria. There were no exclusion criteria.

### Assessment

At 2 years CA, participants underwent a standardized neurological assessment. Participants were assessed in a single session by a trained examiner, who was blinded to the intervention group allocation. Cerebral palsy was diagnosed using standard criteria, including gross motor impairment according to the Gross Motor Function Classification System (GMFCS) [24, 25]. Blindness was diagnosed when vision was worse than 6/60 in the better eye and deafness if amplification or cochlear implant were required. The Bayley Scales of Infant and Toddler Development, Third and Fourth Edition (Bayley-III/Bayley-4) assessed cognitive, language, and motor development [26].

### Outcomes

The primary outcome is survival free of moderate or severe neurodevelopmental impairment. The primary outcome will also be assessed within each stratifying variable: postmenstrual age at birth (< 27 or ≥ 27 weeks), sex, and study hospital. Moderate disability comprises moderate neurodevelopmental delay (Bayley-III/Bayley-4 cognitive, motor, and/or language composite scores < -2 to -3 SDs) or moderate cerebral palsy (walking at 2 years with the need for an assistive technology device, GMFCS level II or III). Severe disability comprises severe neurodevelopmental delay (Bayley-III/Bayley-4 cognitive, motor, and/or language composite scores < -3 SDs) or severe cerebral palsy (not walking at 2 years and not expected to walk, GMFCS level IV and V), blindness, or deafness. Participants for whom disability status cannot be determined (i.e., those with missing data for one or more primary outcome components and no disability on the non-missing components) will be excluded from the primary outcome analysis.

Secondary outcomes include:Death before 2 years of ageRate of mild, moderate, and severe disability. Mild disability comprises mild neurodevelopmental delay (Bayley-III/Bayley-4 cognitive, motor, and/or language composite scores < -1 to -2 SD) or mild cerebral palsy (walking at 2 years without limitations but signs of cerebral palsy, GMFCS I)Mild, moderate, and severe cerebral palsy (GMFCS)Mild, moderate, and severe neurodevelopmental delay (Bayley-III/Bayley-4)Centiles of the Bayley-III/Bayley-4 cognitive, language, and motor composite scoresHead circumference, weight, length, and respective *z*-scores at 2 years of agePartial or exclusive breastfeeding and/or presence of a nasogastric tube or percutaneous endoscopic gastrostomy feeding at 3, 6, and 12 monthsRespiratory support at 2 years of ageOral feeding at 2 years of age

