### Data management

Parents specifically consented to data collection of the current follow-up when they consented to the original TASTE trial. This follow-up study did not involve the collection of biological specimens for storage. Data were sourced from clinical care team notes, medical records, and from parents directly. Each infant has been assigned a study number when recruited to the TASTE trial and data were collected under that study number. Individual participant identifiers apart from study numbers were removed when data were entered onto a paper case record form, then transferred by the data manager to an Excel spreadsheet and stored on a password-protected computer on the Mater Mothers’ Hospital’s computer network. Each data set will be checked by the principal investigator for plausibility and data range checks are applied in the database where appropriate. A data-sharing agreement has been established between the two participating hospitals, and all study group members have access to the final data set.

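### The primary-outcome exclusion rule ignores why a component is missing, so a child too delayed to be scored on the Bayley can be removed rather than counted as impaired

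*Protocol article*

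**What the plan says.** The Outcomes section of the protocol article sets the endpoint: "The primary outcome is survival free of moderate or severe neurodevelopmental impairment". A surviving child can fail it in four ways:

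- a low Bayley score, where any one domain is enough ("Bayley-III/Bayley-4 cognitive, motor, and/or language composite scores < -2 to -3 SDs" for moderate delay, below -3 SD for severe);
- cerebral palsy of at least moderate grade ("moderate cerebral palsy (walking at 2 years with the need for an assistive technology device, GMFCS level II or III"), with GMFCS IV–V as severe and GMFCS I only as mild;
- blindness;
- deafness.

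The same section then deals with incomplete data. The rule covers "Participants for whom disability status cannot be determined (i.e., those with missing data for one or more primary outcome components and no disability" among the components that were observed). Such children "will be excluded from the primary outcome analysis".

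The Assessment section describes a single occasion: "Participants were assessed in a single session by a trained examiner, who was blinded to the intervention group allocation". It gives no alternative for a child who cannot be scored.

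The Statistical methods section keeps every randomized infant in the primary analysis unless consent is withdrawn. It plans multiple imputation under missing at random (MAR), with unspecified sensitivity analyses for departures from that assumption.

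On sources, the Data management section says: "Data were sourced from clinical care team notes, medical records, and from parents directly".

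**The concern.** Delay enters the outcome definition only through a Bayley score, and the exclusion rule asks only whether a component is missing. A child whose delay is too great for the test to be scored therefore has no score that could count as impairment, and the missing score triggers removal. In that case the missingness is caused by the outcome.

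Removing such children raises the reported impairment-free rate in both arms and costs precision. If the share of impaired children lost differs between arms, the treatment effect is biased as well. The study has little room for this: the Sample size section concedes that it cannot reliably detect differences smaller than 13.7 points, and the Discussion expects further loss of power.

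**Working it through.** **The rule, case by case**

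- No Bayley domain scored; no GMFCS II–V, blindness or deafness: a component is missing and no disability is observed, so the child is excluded.
- One domain missing, another completed and below -2 SD: disability is observed, so the child stays in as impaired.
- No Bayley domain scored, GMFCS I cerebral palsy only: this is mild, not moderate or severe. If disability in the rule means disability that counts for the primary outcome, the child is excluded.
- No Bayley domain scored, GMFCS II–V, blindness or deafness: the child stays in as impaired.

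**The two sections side by side**

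Outcomes removes the first and third child from the primary analysis. Statistical methods keeps and imputes them. Both cannot govern. If imputation governs, a MAR model draws the missing status from scored children with similar observed data. With arm as the only predictor, the expected result equals the rate among the children with determined status, so the distortion below would remain. Better predictors would reduce it, but nothing in the model would classify the child as impaired because of the reason for the missing score.

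**Inputs (Sample size section)**

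- Expected participants: 270 × 0.90 = 243, as stated; 121.5 per arm if equal.
- Planned impairment-free rates: 87.7% and 74%; difference 13.7 points. Failures: 12.3% and 26%.
- Design effect from cluster size 1.09 and intra-cluster correlation 0.69: 1 + 0.09 × 0.69 = 1.0621, so effective N = 243/1.0621 = 228.8.
- Assumption, not in the documents: a share f of failures in each arm is untestable and excluded; f = 5%, 10%, 20%.

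**The plan's own power figure**

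With 114.4 effective children per arm, a two-sided 0.05 test (pooled normal approximation) has z = (0.137 × √114.4 − 1.96 × √(2 × 0.8085 × 0.1915)) / √(0.877 × 0.123 + 0.74 × 0.26) = 0.68, which is power of 75.3%. The stated figure of more than 80% is not reproduced two-sided; one-sided gives 84.2%. The present point does not depend on this, and 75.3% serves only as the baseline below.

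**Effect of the exclusion**

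Reported rate = p / (1 − f(1 − p)). Children lost = 121.5 × f × (0.26 + 0.123).

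| f | Lost | Control | Intervention | Difference | Two-sided power |
|---|---|---|---|---|---|
| 0 | 0 | 74.0% | 87.7% | 13.7 | 75.3% |
| 5% | 2.3 | 0.74/0.987 = 75.0% | 0.877/0.99385 = 88.2% | 13.3 | 73.5% |
| 10% | 4.7 | 0.74/0.974 = 76.0% | 0.877/0.9877 = 88.8% | 12.8 | 71.5% |
| 20% | 9.3 | 0.74/0.948 = 78.1% | 0.877/0.9754 = 89.9% | 11.9 (0.8991 − 0.7806 = 0.1185) | 67.2% |

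**Odds ratio**

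The reported odds in an arm are p / ((1 − p)(1 − f)). With equal f the factor cancels and the odds ratio stays at (0.877/0.123)/(0.74/0.26) = 2.51. With unequal shares it is multiplied by (1 − f control)/(1 − f intervention):

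- 20% control, 5% intervention: 2.51 × 0.80/0.95 = 2.11; difference 88.2 − 78.1, about 10.2 points before rounding.
- 5% control, 20% intervention: 2.51 × 0.95/0.80 = 2.97 (from the unrounded 2.505); difference 89.9 − 75.0 = 14.9 points.

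**The case against.** The strongest reply is that the protocol never mentions untestable children and never says that their Bayley is recorded as missing. A scoring convention could sit in an analysis plan or assessment manual that is not shown, and the wrong result arises only if these children are coded as missing. This stands in part: how often the problem occurs, and whether it occurs at all, is unknown. It does not clear the text. The Outcomes section spells out what an undeterminable status is, by missing data alone, and defines delay by scores alone. A convention that counted these children as impaired would have to override the published definition.

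A second reply is that the Statistical methods section promises full inclusion, imputation and sensitivity analyses, and the Discussion adds a table of complete and incomplete participants by arm. This also stands in part: exclusion is not settled, because the two sections disagree. But MAR imputation does not classify these children, and an unspecified sensitivity analysis does not correct the primary result.

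A reader might infer more than the documents support. One such reading is that every child too delayed to finish the Bayley leaves unless cerebral palsy, blindness or deafness is also present. It is wrong on two counts: a single completed domain below -2 SD keeps the child in, and not all cerebral palsy does so. Another is a large bias, for example from taking 5% or 6% of the whole intervention arm as untestable. That would be 5/12.3 = 41% or 6/12.3 = 49% of all failures in that arm, which nothing in the protocol supports.

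**Conclusion.** The point holds as a defect in a stated rule, of modest and unknown size. Read literally, the Outcomes section excludes some children for a reason linked to the outcome. The conflicting Statistical methods section would keep them but not count them as impaired.

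Under equal assumed losses of 5–20% of failures per arm (about 2 to 9 of 243 children), both impairment-free rates are overstated: by 1.0 to 4.1 points in the control arm and 0.5 to 2.2 points in the intervention arm. The difference narrows from 13.7 to 13.3–11.9 points. The odds ratio is then unchanged; it is biased, in either direction, only if the shares differ between arms.

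These figures rest on the planned rates, on equal arms, and on an assumed share that the documents do not give. The share is applied to all failures, which include any deaths. Deaths cannot be lost this way, so the same share of impaired survivors would have a smaller effect.

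**What to change.** 1. Reconcile the Outcomes and Statistical methods sections, so that one statement says who is in the primary analysis and how an undetermined status is handled.
2. Add one sentence to the outcome definition: a child who attended but could not be scored because of the degree of delay counts as impaired in the primary outcome. The reason is judged from the clinical notes already used as a data source, by someone blind to allocation.
3. Treat only non-completion unrelated to ability, such as refusal or lack of time, as missing, and handle it by the planned imputation.
4. Report by arm how many children were classified under this sentence.

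The cost is one sentence and a small blinded review of notes. The downside is some judgement about why a test was not completed. The analysis is described as still to come, so the rule can be fixed before the arms are compared.

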### Sample size

The TASTE trial sample size of 330 infants had 90% power to detect a difference of 0.21 weight *z*-scores at discharge, considering multiples from one pregnancy as a cluster for a 2-sided alternative hypothesis using a generalized estimating equations model. In the TASTE trial, a total of 334 infants were discharged from the hospital and assessed for the primary outcome; however, only 270 of these were eligible for routine clinical follow-up at 2 years CA (< 28 weeks postmenstrual age and/or < 1000 g birth weight). Assuming a similar follow-up rate of 90% to that seen in cohorts at 2 years CA from the Australian state of Victoria, this follow-up study was thus expecting 243 participants. Assuming the same cluster size as for the original study, 1.09, and an intra-cluster correlation of 0.69 (based on that for weight *z*-score at discharge), we have more than 80% power to detect a difference of 13.7% (87.7% smell and taste group, 74% routine care group) at a significance level of 0.05 in the primary outcome of this follow-up study (survival free of moderate or severe neurodevelopmental impairment at 2 years CA) using a logistic generalized estimating equations analysis. A difference of 13.7% would, however, be considered larger than a minimum clinically significant effect but this sample size is not large enough to detect smaller differences reliably [27]. This trial's outcome data could potentially be used in meta-analyses of trials with similar interventions and outcomes, as well as informing the development of future studies.

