### Statistical methods

Statistical analysis will be performed by the authors [name] and [name] with the assistance of other study group members. Data will be exported from an Excel spreadsheet to a statistical package for analysis (Stata 17; College Station, Texas, USA). Data will be analyzed on an intention-to-treat basis. All randomized infants will be included in the primary analysis unless consent has been withdrawn.

There will likely be some substantial missing data as this is a follow-up study. Initially, patterns of missingness of data will be assessed and this information used to determine if missingness is likely to be completely at random (MCAR; missingness is unrelated to values of any known or unknown variable), at random (MAR; missingness of a variable’s values is dependent on known variables other than itself), and not at random (MNAR; missingness depends on the value of the missing value). We plan to use multiple imputation (mi suite of commands in Stata) to impute missing data and jointly analyze the multiple imputed datasets. These methods assume a MAR mechanism of missingness. In practice, it is difficult to definitively show that a variable is MAR rather than MNAR. As such, sensitivity analyses will be performed to see how specific violations of this assumption affect the outcome.

The primary outcome, survival free of moderate or severe neurodevelopmental impairment, and other outcomes with categorical data will be analyzed using a logistic generalized estimating equations analysis (xtlogit Stata command) and subgroup analyses of the primary outcome will be undertaken within each stratum of the stratifying variables (sex, postmenstrual age at birth, birth hospital). Univariate and where appropriate multivariate generalized estimating equations analyses will be used for continuous secondary outcome measures (xtgee command). All outcomes will be assessed against an alternative hypothesis of superiority.

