## Discussion

This neurodevelopmental follow-up study was affected by the COVID-19 pandemic. Melbourne was in prolonged lockdown while Brisbane was affected by extensive travel restrictions and several shorter regional lockdowns. Neurodevelopmental follow-up clinics were never closed, but some study families were unable to travel the required distances, did not attend hospital appointments to avoid potential exposure to COVID-19, or were otherwise affected by the COVID-19 pandemic [28]. These extenuating circumstances impacted this 2-year follow-up study.

During the COVID-19 pandemic, some clinical trials were paused to manage the public health crisis. This follow-up study was embedded into the routine neonatal follow-up program of the respective hospital. Follow-up assessments were not interrupted by public health measures at the Mater Mothers’ Hospital in Brisbane, but at the Royal Women’s Hospital in Melbourne, several prolonged lockdowns made it impossible for trial participants to attend outpatient appointments, or outpatient follow-up was canceled. Therefore, this follow-up study will have missing data, leading to a reduction of statistical power to detect a clinically important difference between groups.

Enrollment of a smaller proportion than planned may result in bias, thus compromising the generalizability of the results. Loss of power will be evaluated and discussed in the final report of the follow-up study. In addition, a table comparing study participants with complete data and those without complete data, stratified by the intervention, will be presented. Regardless of the likely presence of attrition bias, the TASTE trial presents a unique opportunity to obtain longer-term outcomes and may inform the design of future trials.

If missingness of follow-up data is plausibly viewed as *missing completely at random*, meaning that the missingness is independent of any measured or unmeasured participant characteristic, attrition bias is unlikely. If missingness is likely *missing at random*, an appropriate statistical analysis method to control for potential bias, such as inverse-probability weighting or multiple imputations, will be applied. If the missingness is plausibly not missing at random, a definitive bias adjustment may not be possible, and researchers will consider using appropriate sensitivity analysis methods [29].

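### The plan gives two incompatible primary analyses: one drops infants with incomplete data and no observed disability, the other includes and imputes all randomized infants

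*Protocol article*

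**What the plan says.** The protocol article describes the primary analysis set in three places.

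- **Outcomes.** Participants of undetermined disability status are defined, and removed, in one clause: "missing data for one or more primary outcome components and no disability on the non-missing components) will be excluded from the primary outcome analysis".
- **Statistical methods.** "Data will be analyzed on an intention-to-treat basis" and "All randomized infants will be included in the primary analysis unless consent has been withdrawn". On incomplete data: "We plan to use multiple imputation (mi suite of commands in Stata) to impute missing data and jointly analyze the multiple imputed datasets". The section also expects a sizeable problem: "There will likely be some substantial missing data as this is a follow-up study".
- **Discussion.** If data are missing at random, a method "such as inverse-probability weighting or multiple imputations, will be applied". This leaves the choice of method open again.

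The sets of infants also differ. Study design states: "A total of 396 infants were randomized: 196 were assigned to the intervention group, and 200 were assigned to the control group". The abstract describes the follow-up of 334 discharged infants. Sample size says that "only 270 of these were eligible for routine clinical follow-up at 2 years CA", and Eligibility limits the study to survivors who qualify for routine follow-up.

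**The concern.** An infant with a missing component and nothing abnormal on the rest is excluded under Outcomes, but included and imputed under Statistical methods. So is a survivor who missed the whole visit. Nothing in the protocol calls imputation a sensitivity analysis or the exclusion a supplement. Follow-up ended in October 2022, so an unsettled choice could be made with the data in hand.

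The exclusion is also not an ordinary complete-case rule, which would depend on missingness alone. Here, two children with the same gap in their data are treated differently according to what was observed. Because the outcome is survival free of impairment, a known death is a failure with determined status, while an unassessed survivor drops out. Both features push the analysed group towards failures unless missingness itself works the other way.

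**Working it through.** **Inputs from the protocol.** 396 randomized, 334 discharged and 270 eligible for routine follow-up. Expected participants: 270 × 0.90 = 243, which reproduces the stated figure. Planning success rates are 74% (routine care) and 87.7% (smell and taste), so failure rates are 26% and 12.3%.

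**Inputs assumed.** The protocol gives no share with partial data, no chance of detecting disability from partial data and no number of deaths. All three are assumed below.

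**1. How many infants the contradiction reaches.** 396 − 243 = 153 randomized infants lie outside the expected assessed set even at 90% follow-up. Of the discharged infants, 334 − 270 = 64 were outside routine follow-up by design.

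**2. Effect of the exclusion on one arm's rate.** Let p be the true failure rate, m the share with a missing component (unrelated to outcome), and q the share of those who show disability on what was observed.

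Observed rate = [p(1−m) + mq] / [(1−m) + mq], with p = 0.26:

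| m | q = 0.10 | q = 0.20 |
|---|---|---|
| 15% | 0.236/0.865 = 27.3% | 0.251/0.880 = 28.5% |
| 30% | 0.212/0.730 = 29.0% | 0.242/0.760 = 31.8% |

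**3. Effect on the contrast, equal missingness.** Let s be the chance that a true failure with incomplete data is still identified. The rule multiplies the odds of failure by (1−m+ms)/(1−m). With m = 20% and s = 0.5 in both arms:

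- routine care: 0.26 × 0.9 / (0.26 × 0.9 + 0.74 × 0.8) = 0.234/0.826 = 28.3%
- smell and taste: 0.123 × 0.9 / (0.123 × 0.9 + 0.877 × 0.8) = 0.1107/0.8123 = 13.6%

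The risk difference moves from 13.7 to 14.7 points. The odds ratio stays at 0.399, because both arms' odds are multiplied by the same factor.

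**4. Effect on the contrast, unequal missingness.** Take no true effect, 26% in both arms and s = 0.5. With m = 10% in routine care and 30% in smell and taste, the observed rates are 27.1% and 29.9%, a failure odds ratio of 1.15. In the notation of step 2, with q = 0.20 and m = 10% against 20%, the rates are 27.6% and 29.5%, a spurious 1.9 points.

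**5. When the direction changes.** Let missingness be m1 in true failures and m0 in the others. The rate rises only if m1(1−s) < m0. With m1 = 40% and m0 = 20%, there is no change at s = 0.5. At s = 0.25 the rate falls to 0.182/0.774 = 23.5%.

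**6. Deaths kept, unassessed survivors dropped.** Assume 20 deaths and 270 survivors, 22% of them impaired (59.4). The true rate is 79.4/290 = 27.4%. At 75% follow-up it becomes (20 + 44.55)/(20 + 202.5) = 29.0%, and at 60% (20 + 35.64)/(20 + 162) = 30.6%.

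**7. Equal follow-up is not always equal detection.** Deaths are always detected. Assume 10 deaths and 135 survivors per arm, with 35 impaired under routine care and 15 under smell and taste. The true odds ratio is (25/120)/(45/100) = 0.46. At 60% follow-up in both arms it is (19/72)/(31/60) = 0.51, because deaths gain weight.

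**The case against.** The strongest reply has four parts.

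- **Calling a child impaired once any component qualifies is logically correct.** This stands. The fault is in dropping the matching children with normal observed components while also promising to include and impute them.
- **Partial data may be rare.** Assessment took place in a single session, and the Discussion describes missed and cancelled visits, which lose every component. This weakens the size in step 2. The upper end is demanding too: against 22% impairment among survivors, q = 0.20 means about 91% of impaired survivors are detected despite a gap (0.20/0.22). The contradiction is untouched, because a survivor with nothing observed is still excluded by one section and imputed by the other.
- **Keeping known deaths while losing survivors affects any complete-case analysis of this composite.** This also stands. No section says explicitly how deaths enter the analysis set. That they count as failures follows from the outcome definition.
- **The treatment effect may be unaffected.** A reader might infer that the rule biases the planned logistic comparison. The documents do not support that as a general claim. The described losses are geographic, study hospital is a stratifying variable, assessors were blinded, and no figure suggests unequal loss by arm. Step 4 is therefore hypothetical, and bias in the odds ratio needs unequal missingness or detection. A reader might also take inflation as certain, but step 5 shows that it is conditional.

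**Conclusion.** The point holds. The protocol fixes two primary analyses that cannot both be carried out, and they must be reconciled before the primary result is produced. That conclusion rests on the text alone.

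The selection on the observed result is also in the text, but its size is not. If missingness is unrelated to outcome, a true failure rate of 26% would be reported as about 27% to 32% with 15% to 30% partial data. This is an illustration and not a forecast. The odds ratio is preserved when missingness and detection, including detection through death, are equal across arms. Otherwise the contrast is biased, in a direction that the protocol does not allow one to predict.

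**What to change.** Make the analysis in Statistical methods primary and remove the exclusion sentence as the primary rule. Specifically:

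1. Count deaths as failures. In survivors, multiply impute the missing components (the three Bayley composites, GMFCS level, vision and hearing) from allocation, the stratifying variables and the observed components, allowing for multiples. Derive the composite in each imputed data set, then combine.
2. Name imputation as the primary method, so that the Discussion's alternative of weighting does not leave the choice open.
3. State the set to which this applies, reconciling all 396 randomized with the 270 eligible for routine follow-up. One option is to report both the eligible set and the full set. For the 64 discharged infants outside routine follow-up by design, imputation extrapolates to more mature or heavier infants, and the report should say so.
4. Keep a labelled sensitivity analysis of deaths plus survivors with all components observed. Deaths must be named, because a restriction to children with complete components would, read literally, remove them and change the outcome. The determinable-status analysis now in Outcomes can be a second sensitivity analysis if wanted.

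The cost is plan wording and some extra analysis. Imputation is already planned, but component-level imputation with clustered multiples and the additional sets take some work. No new data are needed.
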